Within a previously conducted single-center randomized controlled pilot study performed by the same study group (DRKS-ID: DRKS00004568) 100 patients surgically treated with Milligan-Morgan hemorrhoidectomy have been randomized to be treated either with a postoperative anal tampon (48 patients) or without (52 patients) [25]. The primary endpoint of the study, maximum pain intensity (0–10), has been shown to be significantly lower in patients without tamponade (4.2) than in the group with tamponade dressing after surgery [1, 6] (*p* = 0.001). Complications occurred in 7 patients (15%) in the group with tamponade and in 11 patients in the group without tamponade (21%) (*p* = 0.444), whereas the number of patients with severe anal bleeding was small in both groups (*n* = 2 with tamponade and *n* = 5 without tamponade). Bandage changes were required less often in the group treated without tamponade (*p* = 0.013). The average length of hospital stay was 4 days in both groups.

The results of the pilot study indicate that using tamponade after hemorrhoidectomy significantly increases postoperative pain but has no value in avoiding postoperative bleeding. With the exception of patients on anticoagulants, who have a heightened risk of severe postoperative bleeding, the use of anal tamponade dressings after hemorrhoidectomy seems not to be necessary in routine care.

The results of the pilot study should now be verified by means of a multicenter randomized clinical trial (RCT). This multicenter RCT aims to prove that the established postoperative routine of using tamponade after hemorrhoidectomy has no additional benefit in avoiding postoperative bleeding but leads to significantly more postoperative pain. The NoTamp-study aims to create sufficient evidence base for decision-making on the necessity of using tamponade dressings after hemorrhoidectomy.

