In order to address the primary aim of the study to prove that treating patients without a tamponade dressing after hemorrhoidectomy results in a lower pain burden while the incidence of bleeding requiring surgical revision is no greater than in the patients treated with tamponade (non-inferiority), the primary outcome variables will be examined in terms of an a priori ordered hypothesis at a level of significance of 0.05. Pain values will be described by the mean (SD) and median (IQR). The last observation carried forward (LOCF) method will be used to replace missing values for pain, but only if at least one documentation of postoperative pain is available. Differences in pain will be analyzed using the non-parametric U test (two-sided; alpha = 0.05). If significantly lower pain levels are detected in the treatment arm without tamponade, non-inferiority in the bleeding rate will be also be analyzed at the 5% significance level. Alpha error correction is not required [27]. The incidence of postoperative bleeding needing revision (bleeding rate) will be determined in both treatment arms and will be tested for non-inferiority by calculating the 90% confidence interval (CI) (one-sided hypothesis), with a rate of bleeding two times higher considered acceptable, whereas a bleeding rate three times higher will no longer be considered non-inferior. This rate difference (together with the 90% CI margins) will be considered in relation to the observed revision rate in the control arm. This gives the estimator for the relative increase together with the confidence margins. If the upper limit of this relative increase exceeds 3, then a threefold increase is still possible and non-inferiority is rejected. If the upper limit of this relative increase is < 3, non-inferiority is assumed (with an error rate of 5%). In the unexpected case that the revision rate in the control group is rather low (< 2%) or even 0%, the relative increase will not be calculated. In this case, only the revision rates in the treatment groups are reported (with the 95% CI). The number of patients requiring tamponade in the postoperative course in the group that did not receive primary tamponade after surgery will be presented with the 95% CI.

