Based on the results of the single-center pilot study that demonstrated significant pain reduction (first primary outcome) without tamponade, it can be assumed with great probability that an advantage can also be demonstrated in this much larger multicenter study (first hypothesis). For the second primary outcome based on the results of the pilot study and the international literature it is predicted that 4% of the patients will need surgical revision with tamponade due to severe postoperative bleeding in the treatment group (96% estimated success rate in the control group).

In the intervention group without tamponade a slightly higher rate of bleeding needing surgical revision of ca. 8% is expected. The bleeding rate was 10% in 52 cases included in the pilot study. Therefore, the clinically acceptable and justified limit for non-inferiority is set at 12%, or 8% higher than in the control group with tamponade (8% non-inferiority limit).

Based on these assumptions, the sample size is 433 per group, or 866 patients in total. For study enrollment, assuming a maximum 10% rate of loss to follow up, 953 patients are required. The power was set at 80% in all calculations. Detailed procedures for executing the statistical analysis of the primary and secondary variables and other data will be provided in a statistical analysis plan.

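### The 8-point bleeding limit rests on the pilot's no-tamponade rate and an unexplained threefold bound, and a pass against it cannot show that tamponade gives no protection

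*Protocol article*

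**What the plan says.** All planning figures for the second primary endpoint are in the protocol article, *Statistical analysis and power calculation*. With tamponade, "it is predicted that 4% of the patients will need surgical revision with tamponade due to severe postoperative bleeding". Without it, "a slightly higher rate of bleeding needing surgical revision of ca. 8% is expected". The next sentence reads "The bleeding rate was 10% in 52 cases included in the pilot study", and the limit follows from it: "Therefore, the clinically acceptable and justified limit for non-inferiority is set at 12%, or 8% higher than in the control group with tamponade". The result is 433 per group, 866 in total and 953 enrolled; "The power was set at 80% in all calculations".

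The analysis text of the same section says bleeding will be "tested for non-inferiority by calculating the 90% confidence interval (CI) (one-sided hypothesis"). On what counts as a pass, it describes the test as one "with a rate of bleeding two times higher considered acceptable, whereas a bleeding rate three times higher will no longer be considered non-inferior". It then decides by comparing the upper limit of a relative increase with 3.

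The *Background* identifies the 52 cases as the pilot's arm without tamponade; 48 patients had one. It reports that "the number of patients with severe anal bleeding was small in both groups": 2 with and 5 without.

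Two statements of intent matter. The *Background* sets out to prove that routine tamponade adds nothing to the prevention of bleeding. The statistical section explains non-inferiority as revision bleeding that does not exceed the rate with tamponade.

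**The concern.** The pilot rate without tamponade is the rate of the strategy under test. It shows what happens when tamponade is omitted, not how much extra revision surgery patients should accept. The plan trades more revisions against less pain, because bleeding is tested only after lower pain has been shown, but it never says how large a trade is reasonable or why.

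What is at stake is the conclusion. The limit is twice the excess that the plan itself expects. If a trial can meet it while showing significantly more revisions without tamponade, the result cannot carry a claim that tamponade has no effect on bleeding.

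**Working it through.** **Inputs.** One-sided 5% (90% CI), 80% power, 4% and 8% revision rates, 8-point limit, 1:1 allocation, 433 per arm; pilot 2/48 with and 5/52 without tamponade. All are from the article.

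**1. The plan's sample size.** Unpooled normal approximation:

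n = (z₀.₉₅ + z₀.₈₀)² × [p_C(1−p_C) + p_T(1−p_T)] / (margin − expected excess)²

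= (1.645 + 0.842)² × (0.04×0.96 + 0.08×0.92) / (0.08 − 0.04)² = 432.8, so 433 per group.

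This matches. The trial is sized on an absolute 8-point difference at one-sided 5%.

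**2. The pilot contrast.** 5/52 = 9.6%, 2/48 = 4.2%. The difference is 5.4 points and the ratio 2.3. The Newcombe 95% CI is −5.8 to +16.8 points; Fisher p = 0.44. The limit is 8/5.45 = 1.47 times this difference and 8/4 = 2 times the planned excess.

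**3. How often the 8-point rule passes.** Full binomial enumeration with 433 per arm. Let d = p_T − p_C and SE = √[p_C(1−p_C)/433 + p_T(1−p_T)/433], from the observed rates. Pass if d + 1.645 SE < 0.08. Significantly more revisions without tamponade if d − 1.96 SE > 0. The last column compares the same 90% limit with 4 points.

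| True rates (with v without) | Pass at 8 points | Pass at 8 points and 95% CI above zero | Pass at 4 points |
|---|---|---|---|
| 4% v 4% | 1.000 | 0.024 | 0.911 |
| 4% v 6% | 0.990 | 0.257 | 0.396 |
| 4% v 8% (planned) | 0.795 | 0.503 | 0.055 |
| 4.2% v 9.6% (pilot) | 0.447 | 0.345 | 0.007 |
| 4% v 12% | 0.056 | 0.050 | 0.000 |

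**4. One concrete result.** 18/433 (4.2%) v 40/433 (9.2%): d = 5.08 points, SE = 1.69 points. The upper 90% limit is 5.08 + 1.645×1.69 = 7.9 points, a pass. The lower 95% limit is 5.08 − 1.96×1.69 = +1.8 points, a significant excess without tamponade.

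**5. The rule in the analysis text.** The relative increase can be read in two ways. Control rates below 2% count as no declaration, as the article provides.
- Upper limit of the difference divided by the control rate, below 3: passes with probability about 0.86 at the pilot rates. At 4% v 8%, 0.62 of trials pass with the 95% CI above zero.
- Upper 90% limit of the rate ratio (log scale), below 3: passes with probability about 0.26 at the pilot rates. At 4% v 8%, 0.12 of trials pass with the 95% CI above zero.

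**The case against.** The case for the plan has real substance.

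- **The limit is not simply the test arm's rate.** 12% cannot be computed from 10%; it is 3 × 4%, the threefold bound in the analysis text. The 4% is said to rest on the pilot and the literature. This stands: the document does give a threshold relative to control, but it does not explain it. The full protocol may say more, but the article does state a reason, and that reason does not lead to the limit.
- **Preserving the tamponade effect is the wrong test.** The experimental strategy omits tamponade and so gives up any effect by design. This stands. A limit above the pilot difference is not in itself an error; it needs a judgement of extra revisions against pain.
- **The pilot difference is a poor yardstick.** It rests on 7 events, its interval includes zero, and severe bleeding is not said to equal bleeding that needed revision. This also stands, although the article uses the same figure to set its limit.
- **Acceptable at twofold and excluded at threefold is ordinary design.** Largely so: 8% is the rate the trial is powered to accept and 12% the rate it should rule out. For the same reason a compulsory 4-point test would be a debatable choice. It would fail about 95% of the time under a doubling, which the plan calls acceptable.

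A reader might infer that the rule would pass the pilot's result if it recurred, or that a complete loss of the pilot effect would usually be declared non-inferior. Neither is supported. At exactly the pilot rates with 433 per arm, the upper 90% limit is 8.26 points, which just fails. If those are the true rates, the 8-point rule fails more often than it passes.

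None of this bridges the gap between what a pass shows and what the plan intends to conclude.

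**Conclusion.** The point holds as a mismatch between margin and conclusion, together with a missing rationale. It is not an error in the sample-size arithmetic, nor proof that 8 points is clinically wrong. Under the 8-point rule and the plan's own 4% v 8%, about half of all trials would pass and at the same time show significantly more revisions without tamponade. At the pilot rates about 45% would pass. Such a pass supports only an excess below the margin. It cannot support the aim in the *Background* of showing no bleeding benefit, or the gloss in the statistical section that bleeding is not higher.

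These figures assume 433 evaluable patients per arm, Wald intervals and the difference rule that sizes the trial. The probability of a pass at the pilot rates moves to about 0.86 or 0.26 under the two readings of the relative-increase rule, so the two rules must be reconciled before any single figure applies. Under all three readings, a pass can coincide with a significant excess.

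**What to change.** Keep the sample size and the primary margin, and change the text in four places.

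1. Replace the inference from the pilot's no-tamponade rate with an explicit statement of how much excess revision is tolerated in exchange for less pain, and on what grounds.
2. State that a pass permits one conclusion only: the excess is below the margin. Reword the aims to match.
3. Always report the two-sided confidence interval of the rate difference, and say whether it excludes zero and whether it excludes the pilot's 5.4-point excess. Do not conclude that tamponade has no benefit when the 95% interval excludes zero in favour of tamponade.
4. Reconcile the relative-increase rule with the 8-point difference that gives 433 per group, so that one rule decides.

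Optionally, read the same interval against 4 points as a supportive statement. Nested margins on one interval need no alpha adjustment, and with truly equal rates of 4% this reading succeeds in 91% of trials.

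The cost is a few sentences, with no extra patients, data or alpha. The downside is a less favourable wording of the conclusion if bleeding really rises.

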**Methods:**

We plan to include 953 patients after Milligan-Morgan or Parks hemorrhoidectomy in the NoTamp study. The aim is to demonstrate that using no tamponade dressing after open hemorrhoidectomy is not inferior to using tamponades with respect to postoperative bleeding, and that the patients report less pain. Primary endpoints of the trial are the maximum postoperative pain within 48 h and the incidence of severe postoperative bleeding that requires surgical revision within 7 days after the surgical procedure. Secondary endpoints of the study are the use of analgesics in the postoperative course, the lowest hemoglobin documented within 7 days, quality of life and patient satisfaction. Safety analysis includes all adverse and serious adverse events in relation to the study treatment. Further information can be found in the registration at the German Registry of Clinical Studies (DRKS00011590) and on the study webpage (https://notamp.de/en-GB/trial/main/setLocale/en_GB/). The study is financed by the HELIOS research funding.

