### Statistical analysis and power calculation

The analysis of the primary and secondary endpoints will be performed according to an adapted intention-to-treat (ITT) principle. There will be no interim analysis. The ITT analysis population will include all randomized participants who have undergone the surgical procedure (hemorrhoidectomy). The ITT analysis population will comprise participants assigned to the treatment group based on the randomization schedule, regardless of the treatment actually received. Randomization will be performed up to 12 h prior to the surgical intervention. However, without the surgical intervention there will be no postoperative wound that requires further treatment and thus there will be no data collected and analysis will not be possible. The study participant will therefore be excluded from the clinical trial if the scheduled surgery is not performed. Patients who are excluded from the trial after randomization and before the start of the observation period (postoperative wound care with or without tamponade) are replaced by another study participant in order to achieve the required number of cases. The randomization sequence will be continued. The next patient does not receive the randomized allocation of the excluded patient. The study will be continued until the required number of evaluable patients has been reached. Due to complications it may not be possible to comply with the randomly assigned treatment regimen in a very small number of patients. These patients will not be excluded from the study. Study participants will also be excluded from the clinical trial if a surgical procedure other than Milligan-Morgan or Parks is performed, which does not result in an open wound.

Details of participants’ baseline characteristics including preoperative pain and hemoglobin levels will be provided, but the data will not be compared statistically (by calculating the *p* value) because any differences between groups at this point must arise by chance (if randomized properly).

As a secondary approach, a per-protocol (PP) analysis will be performed excluding patients with any serious protocol deviations, if applicable. The safety analysis will be performed based on the as-treated (AS) population.

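### The enrolment target of 953 adds 10% to 866 instead of dividing by 0.90, so at the stated maximum loss it leaves about 858 evaluable patients (minor arithmetic error)

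*Protocol article*

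**What the plan says.** All of this is in the protocol article. Under *Statistical analysis and power calculation*, the required number is 433 per group, 866 in total. The allowance for attrition follows directly: "For study enrollment, assuming a maximum 10% rate of loss to follow up, 953 patients are required". The Methods part of the Abstract repeats the figure as the planned size of the trial: "We plan to include 953 patients after Milligan-Morgan or Parks hemorrhoidectomy in the NoTamp study".

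The same statistical section has a rule on how long recruitment goes on. Patients who drop out between randomisation and the start of postoperative wound care are replaced, and then: "The study will be continued until the required number of evaluable patients has been reached".

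**The concern.** An allowance for loss to follow-up should give an enrolment number that still leaves the required evaluable number once the assumed share of enrolled patients is lost. Adding 10% to the evaluable number does not do this, because 10% of the larger enrolled number is more than 10% of 866. The plan's figure has exactly the size that this shortcut produces.

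At stake is whether the headline target gives the evaluable number and the power that the article attaches to it. The base calculation has no slack to absorb a shortfall, since 433 per group gives 80.0% power and no more.

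**Working it through.** **Inputs, all from the protocol article**

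- Revision rate with tamponade, 4%: "4% of the patients will need surgical revision with tamponade due to severe postoperative bleeding in the treatment group (96% estimated success rate in the". The parenthesis goes on to name the controls, so this is read as the control rate.
- Revision rate without tamponade, 8%: "In the intervention group without tamponade a slightly higher rate of bleeding needing surgical revision of ca. 8% is expected".
- Margin, 8 percentage points: "limit for non-inferiority is set at 12%, or 8% higher than in the control group with tamponade (8% non-inferiority limit".
- One-sided 5%: "tested for non-inferiority by calculating the 90% confidence interval (CI) (one-sided hypothesis".
- Power: "The power was set at 80% in all calculations".
- Allocation 1:1 (*Design*).
- Loss to follow-up, at most 10%; enrolment 953 (*Statistical analysis and power calculation*).

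**Step 1. Reproduce the base size.** With success rates of 96% and 92%, the distance between the expected difference (4 points) and the margin (8 points) is 0.04. The variance term is 0.96 × 0.04 + 0.92 × 0.08 = 0.0384 + 0.0736 = 0.112.

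n per group = (1.645 + 0.842)² × 0.112 / 0.04² ≈ 433, so 866 in total. This matches the plan exactly. A one-sided 2.5% level would give 550 per group, so one-sided 5% is the level that was used.

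**Step 2. Reproduce the enrolment figure.**

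- 866 × 1.10 = 952.6, rounded up to 953. This is the plan's figure.
- 866 / (1 − 0.10) = 962.2, rounded up to 963. Check: 963 × 0.90 = 866.7, which is enough; 962 × 0.90 = 865.8, which is not.
- Per arm: 433 / 0.90 = 481.1, rounded up to 482, so 964 for equal arms.

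The stated 953 is therefore 10 to 11 patients too low, about 1%.

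**Step 3. What 953 delivers at 10% loss.** 953 × 0.90 = 857.7, about 858. The shortfall is 866 − 857.7 = 8.3, about 8 patients.

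**Step 4. The loss that 953 covers.** 1 − 866/953 = 87/953 = 9.1%.

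**Step 5. Effect on power, within the plan's own sample size calculation.** Power = Φ(0.04 / √(0.112/n) − 1.645), with n per group.

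| n per group | Power |
|---|---|
| 433 (866 evaluable) | 80.0% |
| 428.85 (857.7 evaluable) | 79.7% |

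The loss is about 0.3 percentage points.

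**The case against.** The strongest reply is that the error hardly matters.

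- **Size.** The inputs are much coarser than the error: the intervention rate is given only as approximate, and the pilot study described in the *Background* had 2 and 5 severe bleeds in 48 and 52 patients. A change of 0.3 points in power is far inside that uncertainty. This stands, and it is why the point is minor.
- **Worst case only.** The 10% is called a maximum, follow-up lasts 7 days, and 953 is enough for any loss up to about 9.1%. This also stands, but an allowance for a stated maximum should hold at that maximum, and this one does not.
- **The recruitment rule.** The replacement provision covers only exclusions before the observation period, not later loss to follow-up. The sentence that follows it is worded generally, however. If it is applied, recruitment continues past 953 where needed and neither the shortfall nor the power loss occurs. What remains is that 953 is then too low as the enrolment figure at 10% loss.
- **Which test the power refers to.** The 79.7% belongs to the absolute 8-point margin of the sample size paragraph. The analysis text judges the upper limit of a relative increase against 3. The figure therefore shows the change within the planning calculation and is not the power of that decision rule.

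Two stronger readings are tempting. A reader might infer that 953 enrolled and 866 evaluable are two conflicting stopping points. The article does not support this: it gives 953 as a planned and required enrolment number, nowhere as a cap or stopping rule, and only the evaluable-number sentence says when recruitment ends. A reader might also object that 953 is odd and cannot be split 1:1. A 1:1 allocation ratio stratified by site does not promise exactly equal arms, and a difference of one patient has no analytic effect.

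**Conclusion.** The concern holds as a minor arithmetic error. The stated enrolment figure does not leave the required evaluable number at the stated loss, and both the sample size paragraph and the Abstract carry it.

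The conclusion rests on two assumptions: that the 10% is a share of enrolled patients, which is the ordinary meaning of a loss rate, and that the 866 are patients with evaluable outcomes. The consequence for power depends further on recruitment actually ending at 953 with the full 10% lost. The documents do not show that this will happen, so it should not be said that the trial will be underpowered.

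**What to change.** Restate one figure in the sample size paragraph, and in the Abstract if the number changes. Either option is sound:

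- give 963 patients (964 for equal arms of 482) as the enrolment needed for 866 evaluable at 10% loss; or
- keep 953 and state that it covers a loss of at most about 9.1%, with power of about 79.7% under the planning assumptions if the loss reaches 10%.

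With either option, add a sentence saying that, under the recruitment rule already in the statistical section, the 866 evaluable patients and not the enrolment figure determine the end of recruitment.

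The first option raises the stated target by 10 or 11 patients. The second changes only wording and adds no patients to the target. Neither touches the design or the analysis.
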